### Blood sample collection and biomarker assay

The biomarker CD8⁺-TEMRA cells is analyzed in EDTA-anticoagulated blood samples (up to 2 ml), which are taken in addition to the routine blood tests on admission of the patient (before surgery). All samples are processed and analyzed centrally at the BIH Center for Regenerative Therapies in Berlin to ensure uniform methodology and quality control at all sites. To ensure the integrity of biomarker measurement, blood samples must meet standard pre-analytical conditions, including avoidance of clotting and hemolysis. Study teams at all recruiting centers receive specific training on proper sample handling, focusing on critical factors such as proper fill volume, gentle mixing (to avoid shaking), protection from direct sunlight and appropriate temperature control. The transportation logistics are established and ensure that biomarker measurements can be performed within 24 h of blood collection. It includes two transportation scenarios: Scenario 1) For samples collected between 10:00 am and 5:00 pm, DHL Express is used to ensure delivery to the Berlin lab by 9:00 am the next day. Scenario 2) For samples taken between 17:00 and 22:00 (e.g. from patients requiring urgent surgery), the DHL Same Day Service is used. Samples from the Berlin recruitment centres (Vivantes Klinikum Spandau and Unfallkrankenhaus Berlin) are transported via the Labor Berlin – Charité Vivantes GmbH shuttle system. Upon receipt at the central laboratory, the CD8⁺ TEMRA biomarker (defined as CD45⁺CD3⁺CD8⁺CD57⁺CD28⁻) is determined using the Beckman Coulter DuraClone IM T Cell Subset Tube (Panel B53328), following the manufacturer's protocol. Flow cytometric data are collected and analyzed using Beckman Coulter's Kaluza software. This standardized workflow has been validated in previous studies on different patient groups and demonstrates robust assay performance, with coefficients of variation (CVs) below 10% [25, 31–33].

### Study design

The study is designed as a phase II-III, prospective, multicenter, blinded, national validation study in a realistic (“routine-adapted”) clinical setting. Thus, all study visits are part of the clinical routine, including the radiological and clinical evaluation.

A total of 7 clinical level 1/2 hospitals in Germany are included in the study. To ensure the prospective clinical validation of the CD8 + TEMRA cells as a prognostic marker for disturbed fracture healing, a monitoring of the complete fracture regeneration process is required. Therefore, we calculated a total study time of 52 weeks including 8 clinical visits (Fig. 1).

**Fig. 1 Fig1:**
[figure not shown]
Study Design. At the primary study end point (17–19 weeks), the patients will be classified as normal or delayed healing patients. The latter undergo radiographic/CT analysis at the secondary study endpoint (34–36 weeks) in order to subgroup them into delayed or non-union patients. At the final study time-point (52 weeks), the healing outcome of the non-union will be evaluated via radiographic/CT analysis. Functionality tests and the Short Form 36 Health Survey (SF-36) assessment will be performed with all patients at all study time-points

The initial radiological assessment will be used for the fracture classification and, in addition to the clinical and laboratory findings, the selection of the best surgery intervention method. Adhering to the inclusion and exclusion criteria, we will perform a compatibility assessment, and all eligible patients will be informed about the study content prior to receiving their consent. Blood samples for CD8 + TEMRA cell expression will be taken during the patient´s inhouse admittance prior the surgical intervention. Healing progress will be monitored via clinical/radiological assessment during the following clinical visits. The SF-36 questionnaire will be used to assess the patient’s quality of life. All patient data will be documented via secuTrial software in the electronical case report form (eCRF). Based on healing status of the patients at the primary study end point, subjects will be classified as normal or delayed healers. Normal healing patients will only perform the clinical/functionality tests and SF-36 at the following visits. At the secondary end point, delayed healing patients will be classified further as delayed or non-union according to additional radiographic and clinical evaluation. Whereas the delayed healing patients only perform clinical/functionality tests and SF-36 at the following visit, the non-union patients undergo a final radiographic evaluation at week 52 post injury.

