**Post surgery information (FU visits V4 – V8)**	
Chronic, non-fracture related medication	See “chronic diseases and medication”
Post surgery, fracture related, medication	Usage and duration of vitamin K antagonists, Factor Xa and thrombin inhibitors, acetylsalicylic acid, steroidal anti-inflammatory drugs, non-steroidal anti-inflammatory drugs (NSAID), opioid analgesics
Healing evaluation	X-ray and/or computed tomography, bone consolidated (yes/no), radiographic union scale in tibial fractures (RUST score), radiographic union score for hip (RUSH score), implant set (no/yes; knee joint replacement, hip joint replacement), patient weight-bearing capacity (No load, partial load < 2 kg, 5—10 kg, 10—15 kg, 20 kg, 30 kg, full weight bearing)
X-ray and/or CT images	Storage of the images in eCRF data base
Health economics	Time point of ability to work, payment of sickness benefit, duration and length of physiotherapy units, use of walking aids (armpit supports, walking frame, crutches, rollator), duration of inpatient/partial inpatient stay in a rehabilitation clinic
Patient Reported Outcome Measures	SF-36
Infection status	Pathogen spectrum, medical and/or surgical treatment
Fracture revision treatments	Type and numbers of additive surgical treatment procedures (dynamization, change of procedure within osteosynthesis or to endoprosthesis, use of adjuvants) type and numbers of additive non-surgical fracture treatment procedures (e.g. extended outpatient physiotherapy (EAP), shockwave therapy)

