**Table Taba:** 

Classification	Time post-surgery	Classification criteria
Normal healing	≤ 5 month	Fracture consolidation
Delayed healing	> 5 month and < 9 month	Fracture consolidation or Additional supportive non-invasive treatment or Additive (supportive) surgical treatment
Non-union	> 9–12 month	No fracture consolidation or Additive (supportive) surgical treatment

Incomplete consolidation is defined by one or more of the following criteria: a) presence of resorption zone or incomplete callus formation, b) incomplete bridging (1–3 cortices), or c) no bridging (no cortex is bridged).

Radiographic evidence of bony bridging or complete filling of the fracture gap will serve as the gold standard for biomarker validation.

Radiological signs of bony consolidation are: a) fracture is continuously bridged, b) fracture callus shows homogeneous density, and c) density of the fracture callus is comparable to the cortical density. These signs must be detectable in at least 2 planes. Therefore, the evaluation of the postoperative X-ray images in 2 planes will be used to assess the bony consolidation. If the findings at the primary and/or secondary endpoints are unclear by conventional radiological analysis, the additional performance of a CT scan is medically justifiable and indicated. Furthermore, the RUSH and RUST score will be used to quantify the radiological imaging. Based on the evaluation of the cortices, a RUST score > 10 or a RUSH score > 24 results in consolidation [36–41] (Table 3).

**Table 3 Tab3:** Primary-, secondary- and exploratory endpoints

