**Secondary Efficacy Endpoints:**
1. Successful fracture consolidation at V7 (week 34–36) based on clinical and radiological assessment 2. Time point ability to work 3. RUST/RUSH score at V6, V7, V8

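### The delayed/non-union classes at V7 contradict each other: re-treatment alone makes a patient delayed, un-united untreated patients fit no row, and the non-union window has not yet opened

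*Protocol article*

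**What the plan says.** Five places in the protocol article bear on this point.

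- **Classification table (Outcome measures and clinical endpoints).** The delayed row covers "> 5 month and < 9 month" after surgery and is met by "Fracture consolidation or Additional supportive non-invasive treatment or Additive (supportive) surgical treatment". The non-union row starts after 9 months, runs to 12, and is met by "No fracture consolidation or Additive (supportive) surgical treatment".
- **Study design, text after Fig. 1.** At the secondary endpoint, "delayed healing patients will be classified further as delayed or non-union according to additional radiographic and clinical evaluation". The next sentence sets the later follow-up: "Whereas the delayed healing patients only perform clinical/functionality tests and SF-36 at the following visit, the non-union patients undergo a final radiographic evaluation", timed at week 52.
- **Table 3, secondary endpoints.** The first is "Successful fracture consolidation at V7 (week 34–36) based on clinical and radiological assessment". The third is the RUST/RUSH score at V6, V7 and V8, with no subgroup named.
- **Table 2, post-surgery block for V4 to V8.** It records X-ray or CT, consolidation yes/no and RUST/RUSH, again with no subgroup named. Additive surgical and non-surgical treatments have a separate entry.
- **Abstract, Methods.** The secondary endpoint is placed at nine months, not at weeks 34–36.

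The Study design section also states that "a monitoring of the complete fracture regeneration process is required".

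**The concern.** In the delayed row, treatment stands as an alternative to union. A class that the follow-up schedule treats as needing no further imaging can therefore contain un-united fractures. The non-union row has the same feature, because additive surgery alone also meets it.

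The split matters for the secondary question. The first hypothesis under Aims and Objectives is that the biomarker separates normal, delayed and non-union courses. The Statistical analyses section models delayed healing and non-healing against a final clinical healing classification. If un-united patients are called delayed because they were re-treated, non-union can be under-counted and the delayed group becomes a mixture. A biomarker that does track failure to unite would then look weaker on this contrast. If those patients also have no image at week 52, their radiographic status in months 9–12 is not available to correct the label.

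**Working it through.** **Timing.** Months = weeks × 7 / 30.4375.

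- V7: 34 × 7 / 30.4375 = 7.8 months; 36 × 7 / 30.4375 = 8.3 months.
- Start of the non-union window: 9 × 30.4375 / 7 = week 39.1.
- Final visit: 52 × 7 / 30.4375 = 11.96 months.

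V7 therefore lies inside the delayed window and about 3 to 5 weeks before the non-union window opens (39.1 − 36 = 3.1; 39.1 − 34 = 5.1). Week 52 is the only scheduled visit inside the non-union window. Holding the assessment at exactly nine months, as in the Abstract, would not settle the matter, because the rows read below 9 and above 9.

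**The rules side by side,** for patients classed as delayed at V6:

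| Status at V7 | Class by the table | Class by the Study design rule, if bridging decides | Week-52 image under Study design |
|---|---|---|---|
| Consolidated, with or without re-treatment | delayed | delayed | no |
| Not consolidated, re-treated after month 5 | delayed | non-union | no by the table's class; yes by the evaluation rule |
| Not consolidated, not re-treated | no row applies | non-union | undefined by the table; yes by the evaluation rule |

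The two rules agree only in the first line. In the second they give opposite classes and opposite follow-up. In the third the table gives no class at all. Tables 2 and 3 then list radiographic data at V8 for everyone, which conflicts with the last column wherever it says no.

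**What is not touched.** The primary endpoint is consolidation at V6, before this branch. The sample size rests on the prevalence of delayed healing and reproduces. With z = 2.2414 (two-sided 97.5% interval):

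- Sensitivity: 2.2414² × 0.85 × 0.15 / 0.10² = 64.05 cases; 64.05 / 0.10 = 640.5.
- Specificity: 2.2414² × 0.90 × 0.10 / 0.03² = 502.4 non-cases; 502.4 / 0.90 = 558.2.
- The larger, 640.5, matches the stated 640.

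**Number affected.** The document gives neither the share re-treated between month 5 and V7 (r) nor the share of those un-united at V7 (u). With 640 × 0.10 = 64 expected delayed patients, the number affected is 64 × r × u. Purely by assumption:

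- r = 0.10, u = 0.25: 64 × 0.10 × 0.25 = 1.6 patients (2.5%).
- r = 0.50, u = 0.75: 64 × 0.50 × 0.75 = 24 patients (37.5%).

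A range from about 2 to 24 shows that the size is open. It is not an estimate.

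**The case against.** The best defence is that the Study design section already bases the V7 split on radiographic and clinical evaluation and does not mention treatment received. On that rule, a re-treated patient with an unbridged fracture could be called non-union and imaged at week 52. In addition, Table 3 defines the V7 endpoint as consolidation, the text below the classification table names radiographic bridging or gap filling as the gold standard, and Tables 2 and 3 foresee radiographic data at V8. The performance target concerns the first clinical endpoint, and p-values from secondary analyses are declared exploratory.

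Much of this stands. It shows that the loss of week-52 images is one reading and not a certainty, and it limits the consequence to the secondary question. It does not remove the conflict. The class criteria appear only in the table, and the table gives different answers from the evaluation rule. V8 scores for delayed patients have no planned image behind them if the Study design section is followed. Even with V8 images, the delayed class at V7 would still mix united and un-united patients.

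A reader might infer that these patients end the study with no determined healing outcome. The document does not support that: Fig. 1 has every patient delayed at V6 imaged at V7, so consolidation is known at both visits. A reader might also infer that the surgeon's timing, and not healing, decides who is called non-union. That requires classing the re-treated patient by the table and the untreated one by the evaluation rule; under the table alone the untreated patient has no class.

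**Conclusion.** The inconsistency is real and worth correcting, within limits. The classification table, the V7 split, the V8 imaging schedule and the Abstract's timing cannot all be followed as written. If the table governs, re-treated un-united patients fall in the milder class and may have no radiographic status for months 9–12, so non-union can be under-counted and the delayed versus non-union contrast blurred. If the evaluation rule governs, this particular loss does not occur, but the table is then wrong for V7.

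The effect is confined to the secondary question. No percentage under-count of non-union can be given, because it would also need the number of untreated non-unions, which the document does not state. The Introduction's median of 2 revision procedures does not help, since it says nothing about timing. Nor does the document rank healing courses by severity, so it does not show that the misplaced patients are the worst cases.

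**What to change.** For the secondary biomarker analysis, define the V7 outcome by consolidation status alone: consolidated versus not consolidated at V7, as Table 3 already words the endpoint. Carry additive treatment as a separate variable, since Table 2 already records it. Add a sensitivity analysis that uses the present table's treatment-based classes. This does not require calling anyone non-union at about 8 months against the table's own window.

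The Abstract, the Study design text, the classification table and Tables 2 and 3 must be reconciled on three matters: the classes available at V7, including the patient who fits no row; the start of the non-union window relative to V7; and which patients have radiographic evaluation at V8. Which imaging schedule applies is for the investigators to settle.

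The cost is one extra sensitivity analysis and some redrafting. The count of un-united patients may look less favourable.

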### Data collection

Within the study, the following parameters are recorded and entered into the secuTrial system via electronic case report form (eCRF). The software is compliant to FDA CFR 21 part 11 and, thanks to its web-based design, can be accessed worldwide at any time using any standard internet browser. By this all requirements for the use in studies will be in accordance with the German Drug Law (Arzneimittelgesetz AMG) (Table 2).

**Table 2 Tab2:** Clinical, socio-economic and health data collection of the BioBone study

**Basic data (FU visits 1–3)**	
Date of fracture, date of hospital admission, date of surgery, date of hospital discharge, accident mechanism (vehicle occupant, two-wheeler rider, pedestrian, fall, sports), work accident, age, sex, height, weight, profession	
**Life Style (FU visits 1–3)**	
Smoking status	Smoker, previous smoker, non-smoker
Alcohol consumption	Units/week
Sporting activities	Activity type, h/week,
**Surgery and fracture related information (FU visits 1–3)**	
Number of fractures	1 or ≤ 2
ASA score	I—IV
AO classification	Femur, tibia, humerus, forearm
Degree of soft tissue damage	0—3
Primary surgery (if applicable)	Date, duration, type of fixation (e.g. cast, external fixator)
Final surgery	Date, duration, type of surgery (external fixator, angular stable plate, LISS plate, screw osteosynthesis, intramedullary nail osteosynthesis, compression plate, neutralization plate, others), usage of adjuvants (BMP-2, platelet rich plasma, autologous cancellous bone graft, allogeneic cancellous bone graft, local application of antibiotics, local muscle flap, remote muscle flap, others)
Blood collection	Date and time of pre- and post-surgery blood collection
**Chronic diseases and medication (FU visits 1–8)**	
Osteoporosis	Calcium, bisphosphonates, Vitamin D, SERM, Strontiumrenalat, Teriparatide, antibody-treatment, phosphate, others
Peripheral arterial disease	Grade, walking length, angioplasty, bypass surgery, thrombendarteriectomy, sympathectomy, vasoactive, prostaglandins, others
Heart failure	NYHA class, type of heart failure, pacemaker, heart valve surgery, bypass surgery, coronary heart disease, percutaneous coronary intervention, acetylsalicylic acid, beta-blocker, angiotensin-I-blocker, ACE inhibitors, diuretics, aldosterone antagonists, loop diuretics, osmotic diuretics, thiazide diuretics, potassium-sparing diuretics, transplantation, others
Arterial hypertension	Acetylsalicylic acid, beta blocker, ACE inhibitors, diuretics, calcium antagonists, angiotensin-I-blocker, others
Chronic obstructive pulmonary disease	GOLD classification, cortisone, PDE-4- blocker, prednisolone, acetylcysteine, others
Tumor disease	Type of tumor, tumor surgery, radiation, chemotherapy, antibody therapy, others
Thyroid disorder	Parathyroidectomy, thyroidectomy, hormone therapy, others
Renal failure	Stadium, Peritoneal dialysis, hemodialysis, hemofiltration, cortisol, transplantation, immunosuppressants,
Diabetes mellitus	Type, conventional insulin therapy, oral antidiabetic drugs, intensive conventional insulin therapy, insulin pump therapy, dietary therapy, combined
Rheumatoid disease	Type, non-steroidal anti-inflammatory drugs, steroidal anti-inflammatory drugs, calcineurin inhibitor, cytostatic drugs, antibody therapy, m-TOR inhibitor
Chronic anemia	Substitution
**Post surgery information (FU visits V4 – V8)**	
Chronic, non-fracture related medication	See “chronic diseases and medication”
Post surgery, fracture related, medication	Usage and duration of vitamin K antagonists, Factor Xa and thrombin inhibitors, acetylsalicylic acid, steroidal anti-inflammatory drugs, non-steroidal anti-inflammatory drugs (NSAID), opioid analgesics
Healing evaluation	X-ray and/or computed tomography, bone consolidated (yes/no), radiographic union scale in tibial fractures (RUST score), radiographic union score for hip (RUSH score), implant set (no/yes; knee joint replacement, hip joint replacement), patient weight-bearing capacity (No load, partial load < 2 kg, 5—10 kg, 10—15 kg, 20 kg, 30 kg, full weight bearing)
X-ray and/or CT images	Storage of the images in eCRF data base
Health economics	Time point of ability to work, payment of sickness benefit, duration and length of physiotherapy units, use of walking aids (armpit supports, walking frame, crutches, rollator), duration of inpatient/partial inpatient stay in a rehabilitation clinic
Patient Reported Outcome Measures	SF-36
Infection status	Pathogen spectrum, medical and/or surgical treatment
Fracture revision treatments	Type and numbers of additive surgical treatment procedures (dynamization, change of procedure within osteosynthesis or to endoprosthesis, use of adjuvants) type and numbers of additive non-surgical fracture treatment procedures (e.g. extended outpatient physiotherapy (EAP), shockwave therapy)
**Adverse events/serious adverse events**	
Diagnosis of AE or SAE:	Type AE´s or SAE´s
Duration of AE/SAE:	Start/end/ongoing
SAE:	Yes/no
Severity:	Mild, moderate, severe
Related to study procedure:	Yes/no/unknown
Intervention:	None/concomitant medication/hospitalization/surgical intervention/other
Outcome:	Recovered/recovered with consequences/ permanent without therapy/permanent with therapy/death/unknown

#### Statistical analyses

An optimal cut-off value for circulating CD8 + TEMRA cell levels (> 38%) was determined in a retrospective pilot study [23]. This predefined threshold, alongside an optimized cut-off identified within the multivariable prediction model, will be used to predict the healing outcome of patients. Based on the final clinical healing classification, sensitivity, specificity and other diagnostic accuracy measures will be calculated for CD8 + TEMRA levels within the covariate-adjusted model. CD8 + TEMRA cells level, together with auxiliary covariates and selected confounders, will be entered into a logistic regression model to predict the occurrence of delayed fracture and non-fracture healing beyond the biomarker alone and/or adjusted. Putative key covariates and confounders are age, sex, diabetes type II, NSAID use, rheumatoid arthritis and osteoporosis. Variable selection will be done using the AIC and validated by using bootstrapping methods. The diagnostic ability of the resulting prediction score will be measured using e.g. Nagelkerkes R2N, Somers Dxy, Brier Score and misclassification error. Further, the score will be analyzed by using AUC/ROC curve and the Youden index. Sensitivity, specificity, NPV, PPV, positive LR and negative LR including 95%-confidence intervals will be calculated. Calibration will be evaluated via calibration plot and goodness-of-fit will be tested using Hosmer–Lemeshow-Test and pseudo-R^2^ measures [30].

For missing data, the proportion of missingness will be assessed. If more than 5% of values are missing, multiple imputation (MI) by chained equations (MICE) will be applied under the assumption that data are Missing Completely at Random (MCAR) or Missing at Random (MAR). The imputation model will include all covariates, outcome variables, and relevant auxiliary variables that may inform the missingness mechanism. A minimum of 20 imputations will be generated. To assess the robustness of the results, sensitivity analyses will be conducted by comparing the multiply imputed datasets with complete-case analyses. Additional variables will be analyzed using appropriate parametric or non-parametric statistical tests, depending on scale and distribution. All p-values from secondary analyses will be interpreted in an exploratory, non-confirmatory manner. All statistical analyses will be done using SAS (version 9.4) and R (latest version at time of analysis).

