### Aims and Objectives

The aim is to conduct a prospective, blinded clinical validation study of the CD8 + TEMRA cells as a prognostic biomarker to predict healing outcome after fracture. Aimed test characteristics are a positive predictive value (PPV) > 60% and a specificity > 90%, as well as the clinical routine suitability or cost-effectiveness. We hypothesize that:

The perioperative cut-off level of CD8 + TEMRA cells (> 38%) is a prognostic marker with a high diagnostic accuracy to distinguish between patients with normal-, delayed or incomplete (non-union) fracture healing.Poor bone fracture healing can be predicted with a very high specificity (> 90%) prior to surgical intervention, allowing a more personalized treatment to improve the outcome with high cost effectiveness.As the biomarker reflects the pathogenic impact of TEMRA cells on fracture healing, precise identification of poor healers would offer novel immune-modulatory approaches to improve poor healing.

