#### Sample size calculation

A total number of 640 patients must be completely analyzed. This number is required to simultaneously construct a 97.5%-confidence interval with half-length of 3% for an expected specificity of 90% and a 97.5%-confidence interval with a half-length of 10% for an expected sensitivity of 85% associated with the assumed cut-off and a prevalence of delayed fracture healing of approximately 10%. The 97.5%-confidence intervals are used to maintain a global alpha error of 5%. Assuming a consent rate of 70% among patients meeting all inclusion and exclusion criteria and a dropout rate of 20%, approximately 1,140 patients will need to be screened to enroll 800 participants and obtain 640 complete datasets for analysis. Sample size calculation was done as described by Krummenauer and Kauczor [29]. According to this sample size, we use Harrell's rule that 10 to 20 events per independent predictor variable are necessary to ensure a stable regression model. With the above sample size, approximately 6 predictor variables, respective covariables or confounders 640*0.1/10 can be entered in a final logistic regression model to discriminate regarding the fracture healing outcome [30].

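### Sensitivity and specificity are to be calculated within a covariate-adjusted model, whereas the hypothesis and the sample size concern the biomarker itself at the fixed 38% cut-off

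*Protocol article*

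**What the plan says.** Three parts of the protocol article describe the accuracy of a single marker.

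- **Aims and Objectives** states the hypothesis: "The perioperative cut-off level of CD8 + TEMRA cells (> 38%) is a prognostic marker with a high diagnostic accuracy".
- **Abstract** sets the target: at least 30% of impaired healers identified before surgery, with specificity above 90%. Its sentence on predictive performance attributes sensitivity, specificity, NPV and PPV to the biomarker, measured before surgery and compared with independently assessed healing. That sentence names no covariates.
- **Sample size calculation** sizes the study for 97.5% confidence intervals, one for a specificity of 90% and one "for an expected sensitivity of 85% associated with the assumed cut-off".

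**Statistical analyses** describes something else. On the cut-off: "This predefined threshold, alongside an optimized cut-off identified within the multivariable prediction model, will be used to predict the healing outcome of patients". On accuracy: "sensitivity, specificity and other diagnostic accuracy measures will be calculated for CD8 + TEMRA levels within the covariate-adjusted model". The logistic model is to predict outcome "beyond the biomarker alone and/or adjusted". "Putative key covariates and confounders are age, sex, diabetes type II, NSAID use, rheumatoid arthritis and osteoporosis". Variables are selected by AIC with bootstrap validation, and then "the score will be analyzed by using AUC/ROC curve and the Youden index". Confidence intervals here are 95%.

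**The concern.** The sensitivity and specificity of TEMRA above 38% come from a 2×2 table of test result against healing status. Sensitivity and specificity from a logistic model that also holds age, sex, diabetes, NSAID use, rheumatoid arthritis and osteoporosis belong to a score. They depend on everything in the score, so a marker that adds little could appear to meet the target through its covariates.

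Two further matters follow. With two cut-offs, and the biomarker taken alone and/or adjusted, the text leaves open which result decides whether the marker is validated. And a cut-off chosen and evaluated in the same patients looks better than it will in new ones. At stake is whether the headline result answers the study's own hypothesis.

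**Working it through.** **1. What the 640 was derived for.** Inputs from Sample size calculation: specificity 90% ± 3%, sensitivity 85% ± 10%, two-sided 97.5% intervals (z = 2.2414), prevalence 10%. Formula: n = z² p(1 − p) / d².

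- Sensitivity: 2.2414² × 0.85 × 0.15 / 0.10² = 64.05 impaired healers; 64.05 / 0.10 = 640.5 patients.
- Specificity: 2.2414² × 0.90 × 0.10 / 0.03² = 502.4 normal healers; 502.4 / 0.90 = 558.2 patients.

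The larger governs and reproduces 640. The calculation uses one binary test at one cut-off. No model or covariate enters it.

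**2. Precision if the unadjusted table is primary.** With 64 impaired and 576 normal healers:

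- 97.5% half-length, sensitivity: 2.2414 × √(0.1275/64) = 10.0 points.
- 97.5% half-length, specificity: 2.2414 × √(0.09/576) = 2.8 points.

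The planned precision is met, so the sample size does not change.

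**3. How strong covariates must be to reach the target without the marker.** Assumption: equal-variance binormal ROC curve. Then d′ = z(specificity) + z(sensitivity) and AUC = Φ(d′/√2).

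- Abstract target, 30% at 90%: d′ = 1.282 − 0.524 = 0.757; AUC = Φ(0.535) = 0.704.
- Conversely, AUC 0.75 gives d′ = 0.954 and sensitivity Φ(0.954 − 1.282) = 37% at 90% specificity.
- Sample size assumption, 85% at 90%: d′ = 1.036 + 1.282 = 2.318; AUC = Φ(1.639) ≈ 0.95.

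The risk therefore lies at the 30% target. Covariates alone would need to be extremely strong to reach 85%.

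**4. Illustrative simulation.** None of these inputs except N and prevalence is in the article: N = 640, 10% events, biomarker–age correlation 0.5, one age and one comorbidity covariate, no variable selection, 300 runs. Effects are odds ratios per SD. Sensitivity at 90% specificity is measured in the same data to which the model was fitted.

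| Scenario | Biomarker alone | Model |
|---|---|---|
| A: biomarker no independent effect, covariates 2 | 17% | 36% |
| B: biomarker 2, covariates 1.6 | 33% | 42% |
| C: nothing predicts | 10% | 14% |

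In A the model passes 30% although the biomarker adds nothing. In C the difference is overfitting only.

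**5. Optimism of a fitted cut-off.** In the same simulation the model's cut-off was chosen by the Youden index, which is an assumption. Apparent sensitivity against sensitivity in new patients was 72% v 66% (A), 74% v 67% (B) and 59% v 46% (C), an excess of about 6 to 13 points.

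**The case against.** The case on the other side has real force on several points.

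- **The fixed cut-off is kept.** A reader might infer that the plan replaces the 38% cut-off, or does not validate it. The text does not support that: the predefined threshold is to be used as well, and no ranking of the two is given. What stands is that the text does not say which one decides.
- **Youden.** A reader might also infer that the Youden index selects the cut-off and so conflicts with specificity above 90%. The article lists it only among measures of the score and states no selection rule. Only if it were the rule would the binormal calculation put specificity at Φ(0.757/2) = 65% for the 30%/90% point and Φ(2.318/2) = 88% for 85%/90%.
- **Bootstrap.** Bootstrapping is planned, so internal validation is not absent. The text ties it to variable selection and does not extend it to the cut-off.
- **Another reading.** The sentence on accuracy could mean covariate-adjusted accuracy of the marker, a recognised method that removes the covariates' contribution. This fits poorly with the later sentences, which assess a resulting prediction score. Even so read, the quantity is not the one used for the sample size.
- **Condensed article.** An analysis hierarchy may stand in an analysis plan that is not shown, and silence on it alone would not be a finding. But the article does more than stay silent: it states where accuracy will be calculated, and that statement does not match its own hypothesis and sample size.
- **Size.** The article gives no covariate strength. With weak covariates the inflation could be close to nil.

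**Conclusion.** The point holds in this limited form. The hypothesis, the abstract and the sample size are about the biomarker at the fixed 38% cut-off. The stated analysis takes sensitivity and specificity from a covariate-adjusted model, and sets the fixed cut-off next to an optimised one without naming the deciding result. The mismatch is in the text and needs no assumption.

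The consequences do rest on assumptions. A covariate-only AUC of about 0.70 would meet the 30%/90% target under an equal-variance binormal ROC curve. In the simulation the apparent gain from using the model ranged from about 4 to 19 points, and the optimism of a fitted cut-off from about 6 to 13. The direction is clear: informative covariates raise the score's accuracy above the marker's, and a cut-off tuned and tested in the same data is optimistic. The size in this study is unknown.

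**What to change.** 1. Name one primary analysis: the unadjusted 2×2 table of pre-operative CD8+ TEMRA above 38% against healing status at V6, the primary endpoint in Table 3. Say so explicitly, because Statistical analyses currently refers to the final healing classification.
2. Report its sensitivity and specificity with the 97.5% intervals used in Sample size calculation, and reconcile the 95% stated in Statistical analyses.
3. Make the multivariable model secondary and use it to test added value: covariates alone against covariates plus TEMRA, by likelihood-ratio test and change in AUC.
4. Label any optimised cut-off exploratory. Choose it as the highest sensitivity subject to specificity of at least 90%. Report it only with bootstrap optimism correction that repeats both variable selection and the cut-off search in every resample.

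The cost is wording only, and the sample size stays 640. The change should be made before biomarker results are linked to healing outcomes. The price is that the headline accuracy may look less favourable than a model-based figure.
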